This research is primarily a descriptive epidemiological study looking at the burden of multimorbidity in primary care in England. It will consist of both a cross-sectional, descriptive study of the prevalence of multimorbidity, and a follow-on retrospective cohort analysis investigating the relationship between multimorbidity and health service utilisation. Using a random of sample of 425,400 patient records, we will describe the prevalence of multimorbidity, and will investigate differences in multimorbidity among various sociodemographic covariate groups. Additionally, we will investigate any linkages between mental and physical comorbidities, and patterns of the most common comorbidities.

In the four-year retrospective cohort aspect of our study, we will use regression models to examine how health service utilisation may differ according to the presence of multimorbidity. Our primary outcomes will be the number of GP consultations, the number of prescriptions dispensed, and the number of hospitalisations.

1. **Objectives, Specific Aims and Rationale**

*Please include:*

*(i) The broad research objectives*

*(ii) The specific aims; any hypotheses to be tested should be stated here.*

*(iii) An explanation of how achievement of the specific aims will further the research objectives*

The main objectives of this research are to describe the distribution and patterns of multimorbidity in adults in England, and to investigate the relationship between multimorbidity and health service utilisation. We are also interested in the ways that particular diseases cluster together, because certain comorbidities have been consistently related to increased disease burden and healthcare utilisation^1^.

The selected primary objective of this study is to investigate the burden of multimorbidity in adults in England, which will be established by calculating the prevalence of multimorbidity with 95% confidence intervals. The secondary objective is to describe primary care health service usage in relation to multimorbidity using the number of GP consultations, the number of medication prescriptions dispensed, and the number of hospitalisations.

To meet these objectives, the specific aims of this study in an English general practice population are:

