To meet our secondary objective of investigating health service utilisation in multimorbid patients, we will use a retrospective cohort design. We will create a cohort of patients beginning on January 1, 2012 and following these patients over four years until December 31, 2015. The exposed group will be all patients who have multimorbidity as of January 1, 2012, and the unexposed group will be patients who do not have multimorbidity. We will look at the relationship between the exposure of multimorbidity and the outcome of health service utilisation, which will be assessed based on number of GP consultation, number of prescription medications, and number hospital admissions over the four-year follow-up period. This study design will help us account for the effect of differential mortality that may potentially occur between the exposed and unexposed groups. Mortality will be a secondary outcome in our four-year follow-up. Any patients who have transferred out of their practice during the follow-up period will be censored.

1. **Sample Size**

*Please provide an estimate of sample size, and, where possible, a formal power calculation. An estimate of the expected number of patients available in the CPRD database should normally be included.*

For our primary objective of describing the prevalence of multimorbidity, we have calculated a sample size estimate of 425,400 patients.

This sample size calculation was obtained using the following formula for calculating sample size in cross-sectional studies of prevalence^21^.

$$n=\frac{Z^{2}P\left( 1-P \right)}{d^{2}}$$

In this formula, *n* is the sample size and Z is the test statistic corresponding to a 95% confidence level. P is the expected prevalence of multimorbidity. We set P to be 23.2%, which was the prevalence of multimorbidity obtained by the Barnett *et al.* study on a similar population in Scotland^4^. *d* is the precision of the estimate, corresponding to the effect size. We set size *d* to be 0.13%, which was based on the 95% confidence intervals of the prevalence of multimorbidity from the Barnett, *et al* paper^4^*.*

Using the LSOA “Linked Source Data”, we observed that there are currently 95.2% English patients who have patient level IMD data.  We therefore increased our sample size from 405,000 to 425,400 to account patients who will have to be dropped due to missing IMD data.

1. **Data Linkage Required (if applicable)**

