To meet our fifth aim of determining patterns of multimorbidity associated with health service utilisation outcomes, we will use a latent class analysis (Hagenaars *et al.* 2002) to classify patients according to their distribution of multimorbidities^25^. Within each class of patients, we will assume a distinct multivariable model of health service utilisation outcome. This approach will assist in the identification of class specific factors associated with health service usage. Ideally, we want to fit models including random effects to allow for variation between practices. Depending on the number of classes obtained, this could potentially be quite a big model with a large number of parameters. If appropriate, we will investigate sub-sampling methods for this data set, choosing a suitable representative sample on which to run the chosen models^26^.

1. **Plan for addressing confounding**

*Purely descriptive studies are exempt from this requirement. All other studies should here provide some discussion of what they are doing in the design and/or analysis to control for confounding.*

We will adjust for confounding using multivariable regressions with random-effects models to account for age, sex, socioeconomic deprivation, ethnicity, smoking status, and region, as well as for clustering by GP practice.

1. **Plan for addressing missing data**

*The potential for missing data should be identified and how it will be addressed discussed here.*

We will only use patients with complete age, gender, and IMD data. To reduce the proportion of patients with missing IMD data, we will only use linked practices. Patterns of missingness in the data set will be described and explored at an early stage, and we will consider using multiple imputation techniques where appropriate^27,28^. Missing data for smoking status will be imputed using the last observation carried forward method.

1. **Limitations of the study design, data sources and analytical methods**

*The general limitations of the databases and observational research are well-known. Specific consideration of the potential impact of such limitations should be provided in the context of the proposed study.*

The key limitations to this protocol are as follows:

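### Complete IMD is required for every analysis, so patients without it are left out of an overall prevalence figure that does not need IMD; this is a small, avoidable selection risk

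*Protocol*

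**What the plan says.** The primary objective, under Objectives, Specific Aims and Rationale, is the burden of multimorbidity in English adults, "which will be established by calculating the prevalence of multimorbidity with 95% confidence intervals".

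The Sample Size section sizes the study for the precision of that figure. It reports that "there are currently 95.2% English patients who have patient level IMD data", and says the team "increased our sample size from 405,000 to 425,400 to account patients who will have to be dropped due to missing IMD data".

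The section on missing data then states the rule: "We will only use patients with complete age, gender, and IMD data". It restricts the study to linked practices so that fewer patients lack IMD. It also plans an early look at missingness and leaves multiple imputation open as an option. Nothing there confines the IMD condition to analyses that use deprivation.

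IMD does have a planned role. Aim 1, the covariates listed for the primary objective, and the tests in the Data/Statistical Analysis section all include socioeconomic status, measured by IMD decile.

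**The concern.** Multimorbidity status is defined in Appendix 1 from Read codes, prescriptions and GFR readings. A patient without IMD can be classified as fully as any other, and can be placed in the tables by age, sex, ethnicity, smoking and region. The rule removes such patients from the headline estimate because of a variable that the estimate does not use.

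The plan's answer is to draw more patients. That restores the count, but the extra patients are again people with IMD. If those without IMD differ in multimorbidity, the estimate is shifted by the same amount however many are drawn, and the confidence interval does not show it. Because the interval is planned to be very narrow, a modest difference could matter relative to its width.

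The other provisions do not cover this. With patients lacking IMD excluded, no missing IMD values remain to impute. The four listed limitations concern recording quality and people outside formal registration, unrecorded or undiagnosed disease, coding of contact type, and severity. None mentions registered patients whom the study itself drops.

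**Working it through.** **Inputs.** From the Sample Size section: Z = 1.96 (95% level), P = 23.2%, d = 0.13 percentage points, IMD present in 95.2% of English patients, 405,000 inflated to 425,400. The missing share is m = 1 − 0.952 = 0.048. The documents give no prevalence for patients without IMD, so every gap used below is an assumption.

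**1. The plan's own sample size.** n = Z²P(1−P)/d² = 3.8416 × 0.232 × 0.768 / 0.0013² = 405,018 (405,003 with unrounded Z). The stated 405,000 reproduces.

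**2. The inflation.** 405,000 / 0.952 = 425,420. The stated 425,400 reproduces, and the form of the inflation is correct.

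**3. Precision with and without the exclusion.** Expected exclusions are 425,400 × 0.048 = 20,419, leaving 404,981. The half-width is 1.96 × √(0.232 × 0.768 / N):

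- N = 404,981 (patients without IMD dropped): 0.130 points, as planned.
- N = 425,400 (everyone kept): 0.127 points.

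The exclusion costs about 0.003 points of half-width, which is negligible.

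**4. Bias from the exclusion.** Let p₁ be the prevalence with IMD and p₀ the prevalence without. Prevalence in everyone sampled is (1−m)p₁ + m·p₀. The plan reports p₁, so

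bias = p₁ − [(1−m)p₁ + m·p₀] = m(p₁ − p₀) = 0.048 × (p₁ − p₀).

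With p₁ = 23.2%:

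| Assumed prevalence without IMD | Gap p₁ − p₀ (points) | Bias (points) |
| --- | --- | --- |
| 10% | 13.2 | +0.63 |
| 18.2% | 5.0 | +0.24 |
| 20% | 3.2 | +0.15 |
| 23.2% | 0 | 0 |
| 26% | −2.8 | −0.13 |
| 28.2% | −5.0 | −0.24 |
| 35% | −11.8 | −0.57 |

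**5. Gap at which bias equals the half-width.** 0.13 / 0.048 = 2.7 points, in either direction.

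**6. Relative size.** A 5-point gap shifts the estimate by 0.24 points, and 0.24 / 23.2 = 1.0%.

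**7. If fewer patients lack IMD.** With an assumed missing share of 2%, the gap needed is 0.13 / 0.02 = 6.5 points. With 1%, it is 13 points.

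**The case against.** The strongest reply is that one analysis cohort with a common denominator is a legitimate choice, and that the loss was foreseen and compensated. Both statements are right, and step 3 confirms the second. A reader might infer from the 4.8% exclusion that the study loses needed sample size or precision. The documents do not support that.

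A reader might also infer that IMD plays no part in the primary objective. That is wrong too: IMD decile is a stated covariate there and a planned stratifier in Aim 1. Only the overall figure and the non-IMD breakdowns are free of it.

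Three further points limit the concern:

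- The 4.8% is a planning figure for English patients. The protocol does not say whether it was taken before or after the restriction to linked practices, so the realised share may be smaller.
- The protocol gives no reason why IMD is missing and no prevalence for those patients. It is tempting to suppose that they are recent movers, but the Study Design section already requires 12 months of registration before January 1, 2012, so that explanation fits poorly.
- The value 0.13 is a sampling half-width borrowed from an earlier study's interval, not a threshold of practical importance. Differences in how morbidities are defined may matter far more: the Background cites prevalences of 16% and 23.3% and attributes discrepancies largely to definitions.

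The planned early look at missingness could accommodate a comparison of patients with and without IMD. It would not by itself change the stated rule that removes them from the estimate.

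**Conclusion.** The point holds as a possible selection bias in the overall prevalence and the non-IMD breakdowns, created by a rule that those estimates do not need. Its size is 0.048 × (prevalence with IMD minus prevalence without), on the plan's own missing share, and less if linked practices have more complete IMD. Direction and magnitude cannot be determined from the documents. An assumed gap of about 2.7 points would match the planned half-width. An assumed 5-point gap would shift the estimate by 0.24 points, about 1% of its value. The documents do not show that the estimate is in fact biased, and a reader should not conclude that it is. The point is minor, but the selection is avoidable and the listed limitations do not mention it.

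**What to change.** In the missing-data section, limit the IMD-completeness condition to analyses that use IMD. Then:

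- Report the overall prevalence in all sampled patients with known age and sex, either as the main figure or at minimum as a sensitivity analysis beside the IMD-complete cohort. The breakdowns by age, sex, ethnicity, smoking and region can be handled in the same way.
- Compare patients with and without IMD on age, sex and multimorbidity, and state the realised share without IMD.
- Leave IMD-stratified and IMD-adjusted analyses on the IMD-complete cohort.

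The cost is a change of wording, an analysis flag and one short comparison table. Denominators will differ between IMD and non-IMD tables and should be labelled. The extract must also retain patients without IMD. The Sample Size section implies that they are drawn and then dropped, but the protocol does not say that their records are kept, so this needs confirming.

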**Appendices**

Appendices should be used for essential supporting information only (e.g. code-lists) and they must be cited within the body of the protocol.

**Appendix 1: List of the 36 disease conditions to be included in multimorbidity count**

| Code | Condition | *Criteria* |
| --- | --- | --- |
|  |  |  |
| HYP | Hypertension | *Read Code ever recorded* |
| DEP | Depression and Anxiety | *Read code recorded in last 12 months OR >=4 anti-depressant prescriptions (excluding low dose tricyclics) in last 12 months OR >=4 anxiolytic/hypnotic prescriptions in the last 12 months* |
| PNC | Painful condition | *>=4 POM analgesics in last 12 months OR >= 4 specified anti-epileptics in the absence of an epilepsy Read code in last 12 months* |
| AST | Asthma (currently treated) | *Read code ever recorded AND any asthma prescription in the last 12 months.* |
| CHD | Coronary heart disease | *Read Code ever recorded* |
| DIB | Diabetes | *Read Code ever recorded* |
| THY | Thyroid disorders | *Read Code ever recorded* |
| RHE | Rheumatoid arthritis, other inflammatory polyarthropathies & systematic connective tissue disorders | *Read Code ever recorded* |
| HEL | Hearing loss | *Read Code ever recorded* |
| COP | COPD | *Read Code ever recorded* |
| IBS | Irritable bowel syndrome | *Read code ever recorded OR ≥ 4 prescription only medicine antispasmodic prescription* |
| CAN | New diagnosis of cancer in last five years | *Read code first recorded in last 5 years* |
| ALC | Alcohol problems | *Read Code ever recorded* |
| OPS | Other psychoactive substance misuse | *Read Code ever recorded* |
| CON | Constipation (Treated) | *≥4 laxative prescriptions in last year* |
| STR | Stroke & transient ischaemic attack | *Read Code ever recorded* |
| CKD | Chronic kidney disease | *Best of the last 2 GFR readings <60* |
| DIV | Diverticular disease of intestine | *Read code ever recorded* |
| ATR | Atrial fibrillation | *Read code ever recorded* |
| PVD | Peripheral vascular disease | *Read code ever recorded* |
| HEF | Heart failure | *Read code ever recorded* |
| PRO | Prostate disorders | *Read code ever recorded* |
| EPI | Epilepsy (currently treated) | *Read code ever recorded AND antiepileptic prescription in last 12 months* |
| DEM | Dementia | *Read code ever recorded* |
| SCZ | Schizophrenia (and related non-organic psychosis) or bipolar disorder | *Read code ever recorded/recorded in last 12 months OR Lithium prescribed in last 168 days* |
| PSO | Psoriasis or eczema | *Read code ever recorded AND ≥ 4 related prescriptions in last 12 months (excluding simple emollients)* |
| IBD | Inflammatory bowel disease | *Read code ever recorded* |
| MIG | Migraine | *≥ 4 prescription-only anti-migraine prescriptions in last year* |
| BLI | Blindness and low vision | *Read code ever recorded* |
| SIN | Chronic sinusitis | *Read code ever recorded* |
| LEA | Learning disability | *Read code ever recorded* |
| ANO | Anorexia or bulimia | *Read code ever recorded* |
| BRO | Bronchiectasis | *Read code ever recorded* |
| PRK | Parkinson’s disease | *Read code ever recorded* |
| MSC | Multiple sclerosis | *Read code ever recorded* |
| CLD | Chronic Liver Disease and Viral Hepatitis | *Read code ever recorded* |

**Appendix 2: Morbidities included in Barnett *et al.,* excluded from this study**

| Condition | Reason for exclusion |
| --- | --- |
| Treated Dyspepsia | No valid set of codes developed due to increasing use of proton pump inhibitors use to prevent gastric side effects of medications |
| Anxiety | Significant overlap with depression, therefore combined with depression to form Depression and Anxiety comorbidity |
| Glaucoma | Significant overlap with visual impairment, thus little added value as a separate comorbidity. |
| Viral Hepatitis | Significant overlap with Liver Disease, therefore combined with Liver Disease to form Chronic Liver Disease and Viral Hepatitis comorbidity |

**Appendix 3: Sample Code lists to be used for selecting comorbidities**

| **Disease** | **Code Type** | **Codes** |
| --- | --- | --- |
| Hypertension | Diagnosis | 204,799,351,15377,1894,4372,83473,10818,3712,7329,31755,59383,73293,57288,25371,51635,34744,16059,31387,31341,42229,18765,7057,69753,102458 |
| Asthma | Diagnosis | 5867,22752,73522,41017,11370,80085,74025,75049,74093,81364,74778,74627,84312,77881,83552,79714,74381,86315,74588,81113,74348,81835,78930,84251,76765,78239,74500,10487,3458,3018,13065,3366,84275,5798,78,1555,7146,2290,1208,15248,7731,14777,5627,27926,6707,45782,5267,3665,29325,58196,18323,45073,25796,185,40823,4442,32727,4892,233,232,8335,12987,16070,4606,21232,18207,93353,39478,47684,74458 |
|  | Medication | 10090,10102,10218,10254,10289,10321,10331,10360,10407,10432,10433,10458,10561,10597,10723,10744,10812,10813,10831,1087,1093,10958,10968,1097,1100,11046,11198,11307,11410,11478,11497,11588,11618,11719,11732,11779,11993,12042,12144,12240,12274,1236,1242,1243,1258,1259,12633,1269,12699,12808,12822,12909,12994,13037,13038,13040,13181,13256,13273,13290,13307,13365,1346,13529,13575,13757,13815,13996,1406,1409,1410,1411,1412,1414,1415,1422,1423,1424,1426,14294,14306,14321,14448,14483,14524,14525,14527,14561,14567,14590,14603,14700,14736,14739,14757,14991,15025,15153,1518,15284,15326,15365,1537,15409,15441,15483,1551,1552,15613,15706,15765,16018,16054,16148,16151,16158,1619,1620,16207,1628,1629,1630,16305,1635,1642,16433,16577,16584,16625,1676,1680,1683,1697,1698,16994,17,17002,1711,17140,17185,1725,1727,1728,1734,1741,17465,17590,17654,17670,17696,17874,17875,1794,1801,18140,18288,18299,18308,18314,1832,1833,1834,18394,18421,18456,18484,18537,1861,18622,1882,18848,1885,18968,18988,19031,19121,19350,19376,19389,19401,1950,1951,1952,1956,1957,1959,1960,1961,1962,1974,1975,20171,2020,20225,20825,20838,2092,21005,21102,21224,2125,2147,2148,21482,2152,2158,2159,2160,21769,218,21859,22080,2224,2229,22313,22430,2282,23269,2335,235,23567,23572,23709,23741,2395,23961,24023,24117,24207,24380,2440,24418,24674,24898,25022,25119,25125,25204,25339,25784,25937,2600,26063,2609,2655,26616,26860,26873,26987,27188,2722,2723,27249,273,27340,27505,2757,2758,27593,27679,27842,27944,28073,282,28241,2850,28508,2851,28577,2862,28640,2869,28761,28881,2892,2893,2911,29267,29273,29325,29475,2951,2978,2992,2994,2995,30118,3018,30204,30210,30212,30229,30230,30238,30240,30596,30649,3075,31,31082,3119,31231,314,3150,3163,31774,31845,3187,31933,32050,32102,3220,3254,32874,3289,32893,3297,3305,3306,33089,33258,33373,33588,3363,3374,33817,33849,3388,34018,34029,34134,34162,34310,34311,34315,34428,3443,34618,34619,34702,34739,34794,34859,34919,34995,35000,35011,35014,3546,35510,35522,35557,3556,35602,35631,3570,35724,35744,3585,35862,3666,3688,3743,37612,37615,3763,37791,3786,3787,38,38097,38120,3838,38416,38419,3927,3947,3989,3993,3994,40177,4055,40655,40709,4100,41269,4131,4132,41412,41549,41691,4171,41832,4222,42497,42511,4268,42910,4306,4365,4413,44713,4497,4499,4514,454,4541,4545,45863,4591,4592,4593,4601,46157,4634,4640,4647,465,4665,4688,4759,4801,4803,4842,4926,4942,510,5143,5161,5170,5172,5185,5223,5261,5308,5309,534,5453,549,5516,5521,5522,555,5551,5558,556,5580,5683,5718,5740,5753,5804,5822,5837,5864,5885,5889,5898,590,5941,5942,5975,5992,6050,6081,6315,6325,638,6462,6512,6522,6526,6569,6616,665,6719,674,6746,6758,6772,6780,6796,6839,6911,6938,696,6988,7013,7017,7133,7140,719,7192,7268,7270,7356,746,7576,7602,7638,7653,7711,7730,7731,7732,7733,7788,7832,7841,7891,7935,7948,7954,7964,7965,7972,8,8056,8057,8111,8215,8267,8333,8339,8433,8470,8498,8522,856,8608,8610,862,863,8635,8653,8676,879,880,8806,881,882,883,895,8955,896,898,907,908,909,9092,910,911,9164,9233,9270,9384,942,947,9477,956,957,9571,9577,958,959,9599,960,9635,964,9651,9681,9711,987,99,9921 |
| Heart Failure | Diagnosis | 101138,101137,106897,12550,104333 |

**Amendment 1**

Text from this amendment, which was placed inside the protocol in blue, has been set to black to indicate that it is not new, but copied here for reference.

From the background section:

*In the current literature, there is no consensus on how to define multimorbidity*^4,15^. *A 2013 systematic review of 39 studies of the prevalence, patterns, and determinants of multimorbidity in primary care found that the number of health conditions that these studies defined as multimorbidity ranged form 5 conditions to 335 conditions*^15^*. To create a list of comorbidities that identify patients with multimorbidity in primary care, the Cambridge Primary Care Unit has drawn on the work of Barnett et al. to develop a list of chronic diseases and long-term illnesses that have face value validity as entities that contribute to multimorbidity in primary care. See Appendix 1 for the list of these morbidities and for the criterion that will be used to define these diseases and conditions. The Barnett et al. multimorbidity list was initially developed based on recommendations obtained from a systematic review of comorbidities relating to cardiovascular disease*^16^*, from the UK Quality and Outcomes Framework*^17^*, and from important long term disorders that have been identified by NHS Scotland*^4,18^*. We have chosen to use the Barnett et al. list as the baseline from which to build our list of morbidities for a number of reasons. First, the selection of comorbidities in this list is based on clinical relevance rather than their usefulness to predict outcomes*^4^*. We believe this focus on clinical relevance provides the most meaningful description of the epidemiology of multimorbidity in primary care. In contrast, some multimorbidity scores such as the Charlson score aim to predict mortality, and often only include conditions that improve predictability*^19,20^*. As a result, these existing predictive measures such as the Charlson score are not as clinically meaningful for describing multimorbidity in general practice as. Additionally, the Barnett et al. list consists of comorbidities that are relevant to the Scottish population, which makes them likely to be relevant in the English population*

*Three morbidities, treated dyspepsia, anxiety, and glaucoma, were present on the Barnett list, but were excluded from this study. See Appendix 2 for the specific rationale of exclusion.*

*The specific Read code lists for extracting comorbidities are being developed using existing published lists of codes including clinicalcodes.org, CALIBER, NHS Scotland’s Information Services Division, and conditions incentivized under the Quality and Outcomes Framework, and new lists drawn from all possible codes within CPRD. Two clinicians will review each set of codes and, when disagreement is present, additional input from the other two clinicians will be used. Additionally, an estimate of the general population prevalence of the comorbidity will be calculated using the selected codes and a sample of CPRD data, and compared with previous epidemiologic studies. See Appendix 3 for sample code lists for hypertension, asthma, and heart failure.*

From study design:

*We will take a random sample of 425,400 patients registered to English General Practices that have provided “research standard” data continuously from January, 2012 until December, 2015. All adult patients (≥18 years of age)* *from practices meeting this acceptable data quality criteria and who have been registered for at least 12 months prior to* *January 1, 2012* will be included to create a random sample of 425,400 patients.

*To meet our secondary objective of investigating health service utilisation in multimorbid patients, we will use a retrospective cohort design. We will create a cohort of patients beginning on January 1, 2012 and following these patients over four years until December 31, 2015. The exposed group will be all patients who have multimorbidity as of January 1, 2012, and the unexposed group will be patients who do not have multimorbidity. We will look at the relationship between the exposure of multimorbidity and the outcome of health service utilisation, which will be assessed based on number of GP consultation, number of prescription medications, and number hospital admissions over the four-year follow-up period. This study design will help us account for the effect of differential mortality that may potentially occur between the exposed and unexposed groups. Mortality will be a secondary outcome in our four-year follow-up. Any patients who have transferred out of their practice during the follow-up period will be censored.*

From exposures and outcomes:

*See Section D for the rationale for choosing these specific morbidities.*

*We will consider mortality as a secondary outcome of the retrospective cohort component of our study.*

From Data/Statistical analysis:

*These pairs will be identified by calculating the prevalence for all 630 (* $\frac{36*35}{2}$*) potential disease couplets, and then reporting the comorbidity pairs with >5% prevalence. As this is a descriptive study, we are primarily interested in identifying the most commonly occurring disease couplets, and describing their prevalence. Clinical appraisal of the most prevalent couplets will be conducted to establish whether these pairs are common because of a causal link, or common because each has relatively high prevalence. These differences will be addressed in our discussion.*

*In this analysis, we will adjust for patients who died during the four-year follow-up as well as for patients who have been censored due as a result of transferring out of the practice. We will use a Cox proportional hazards model to describe the differences in mortality rate between exposed multimorbidity patients and non-multimorbid patients.*

H. Data Linkage Required (if applicable)

*Please provide a synopsis of the purpose(s) for which the each of the linkages requested in section 18 of the application form is required.*

The proposed linkage of GOLD data to the patient-level Index of Multiple Deprivation (IMD) dataset will enable us to obtain an estimate of socioeconomic status, which we consider a key predictor of multimorbidity^4,5,22^. The proposed linkage to the Integrated Hospital Episode Statistics (HES) datasets will allow us to obtain much more complete ethnicity data^23^, which we believe to be an important predictor of multimorbidity that has not been adequately addressed in the current literature^24^. It will also allow us to obtain information about the number of hospital admissions, which is one of our outcomes for measuring health service utilisation.

